## Abstract

**Background:**

Rectal cancer surgery is accompanied with high morbidity and poor long term functional outcome. Screening programs have shown a shift towards more early staged cancers. Patients with early rectal cancer can potentially benefit significantly from rectal preserving therapy. For the earliest stage cancers, local excision is sufficient when the risk of lymph node disease and subsequent recurrence is below 5 %. However, the majority of early cancers are associated with an intermediate risk of lymph node involvement (5–20 %) suggesting that local excision alone is not sufficient, while completion radical surgery, which is currently standard of care, could be a substantial overtreatment for this group of patients.

**Methods/Study design:**

In this multicentre randomised trial, patients with an intermediate risk T1-2 rectal cancer, that has been locally excised using an endoluminal technique, will be randomized between adjuvant chemo-radiotherapylimited to the mesorectum and standard completion total mesorectal excision (TME). To strictly monitor the risk of locoregional recurrence in the experimental arm and enable early salvage surgery, there will be additional follow up with frequent MRI and endoscopy. The primary outcome of the study is three-year local recurrence rate. Secondary outcomes are morbidity, disease free and overall survival, stoma rate, functional outcomes, health related quality of life and costs. The design is a non inferiority study with a total sample size of 302 patients.

**Discussion:**

The results of the TESAR trial will potentially demonstrate that adjuvant chemoradiotherapy is an oncological safe treatment option in patients who are confronted with the difficult clinical dilemma of a radically removed intermediate risk early rectal cancer by polypectomy or transanal surgery that is conventionally treated with subsequent radical surgery. Preserving the rectum using adjuvant radiotherapy is expected to significantly improve morbidity, function and quality of life if compared to completion TME surgery.

**Trial registration:**

NCT02371304, registration date: February 2015

## Background

The introduction of population based screening programs for colorectal cancer is expected to cause a shift towards more early stage carcinoma’s, as shown in the United Kingdom [1]. Radical rectal surgery (i.e. low anterior resection (LAR) or abdominoperineal resection (APR)) is accompanied with high operative morbidity of 36 % and is associated with a significant negative impact on functional outcome and quality of life [2–4]. More than 50 % of patients experience some form of faecal incontinence with a negative impact on quality of life. Urinary incontinence or retention and sexual dysfunction are common [2, 5–7]. Furthermore, patients after total mesorectal excision (TME) are confronted with stoma related difficulties, morbidity and subsequent hazards from stoma reversal in those with protected low anastomoses. In the Dutch TME-trial, 19 % of patients did not have a reversal of a temporary stoma after LAR and the overall long term or permanent stoma rate was 40 % [8]. After APR, up to 40 % of patients experience perineal wound complications. Long-term discomfort after APR is related to stoma and stoma appliance-related complications, occurring in up to 66 % [9]. The disadvantages of radical surgery have been acceptable in the pursuit of oncological control. However, early stage cancer might be amenable to cure by local excision with avoidance of radical surgery with its negative impact in a significant proportion of patients [10]. Local excision alone has only been considered oncological safe for low risk T1 rectal cancer, which may be defined as well/moderately differentiated without lymphatic or vascular invasion and excised with at least 1 mm margin. In case of any unfavourable histological characteristic, there is a substantial increase in the risk of lymph node metastases with impaired oncological outcome after local excision alone, requiring completion total mesorectal excision (TME) [11]. Histological characteristics which are associated with increased risk of local recurrence are: poor differentiation, deep submucosal infiltration, lymphatic or vascular invasion, SM3 and tumour size > 5 cm for pT1 or > 3 cm for pT2 [11, 12].

Early rectal cancer (T1 and T2) with intermediate risk for recurrence make up to 75 % of locally excised rectal cancer, and present a management dilemma for patient, surgeon and oncologist. These patients could be treated with additional chemo-radiotherapy, thereby preserving their rectum which likely has a positive impact on function and quality of life (HRQoL). Additional chemo-radiotherapy in the intermediate risk group has a potential to decrease the risk of local recurrence by sterilizing mesorectal lymph nodes in the vicinity of the excised tumour that may harbour (micro)metastasis. Current evidence on rectal preserving treatment options after local excision is limited, because of small sized retrospective studies with several methodological problems. Characteristics of included patients, surgical technique of local excision, and reported local recurrence rates and survival after adjuvant chemoradiotherapy for pT1-T2 carcinomas are highly variable [13–18]. We conducted a systematic review of all these studies, showing poor quality of the selected studies with lack of randomised data ([name] et al.). A relatively high pooled weighted average of local recurrence rate of 14 % after adjuvant radiotherapy was found, probably related to inclusion criteria that were not confined to an intermediate risk group. Only two of the 14 included studies in the review consisted of a patient population that all had clear resection margins [19, 20]. Their pooled average of 6 % recurrence after adjuvant chemoradiotherapy therapy is low, but the sample size (*n* = 27) was too small to draw any conclusion. Using strict patient selection based on MRI imaging to exclude patients with suspicious lymph nodes and pathological assessment of the excised tumour, adjuvant (chemo)radiotherapy is potentially a valid option as curative completion treatment for radically excised pT1 and small pT2. Additionally, improvements in MRI and advanced endoscopic imaging will enable careful follow-up and early detection of locoregional recurrent disease, allowing for early salvage surgery that offers acceptable oncological outcome [21].

Therefore, there is an urgent need to define a new treatment approach for patients who are confronted with invasive growth in a locally excised rectal lesion with intermediate risk of lymph node metastases. Such an approach should result in an optimal balance between treatment related morbidity and oncological control for these early stage carcinomas. A multicentre randomised controlled trial with strict inclusion criteria based on tumour characteristics and an intensive follow-up schedule in the rectal preserving treatment arm could provide the much needed evidence on oncologic outcome after adjuvant chemoradiotherapy for locally excised rectal cancer compared to standard completion TME.

## Methods/Design

The main objective of this multicentre randomised controlled trial is to determine the optimal treatment strategy for patients with a locally excised rectal lesion revealing an early stage rectal cancer with post excision pathology predicting intermediate (5–20 %) risk of recurrence. The patients will be randomised, after local excision, between either adjuvant chemoradiotherapy or standard completion TME surgery.

The TESAR trial hypothesizes that local excision combined with adjuvant chemoradiotherapy and close-surveillance with the possibility of early salvage surgery is non-inferior to completion TME in terms of local recurrence and superior in terms of treatment related morbidity, functional outcome, and HRQoL.

All pathology specimens of potentially eligible patients will be centrally revised by one pathologist in order to exclude inter-observer bias. The patient who meets all the inclusion criteria without any of the exclusion criteria will be given information about the proposed trial. The patient will have at least three days to decide upon study participation. Randomization will be performed by a central automated randomization system using the trial website, with stratification for age (75- and 75+), ASA (I and II+) classification, initial treatment (full thickness excision and endoscopic excision) and tumour classification (high risk T1 and low risk T2). The treatment, either adjuvant chemo-radiotherapy or completion TME surgery, should start within 4–8 weeks from randomisation. Randomisation will be performed in random blocks of sizes and 4.

The primary aim of the TESAR-Trial:To compare rectal preserving therapy (local excision followed by adjuvant chemoradiotherapy) with completion TME surgery in terms of 3-year locoregional recurrence rate.

Secondary aims of the study are:To compare treatment related morbidity between the study arms, both short and long-term.To determine 3-year and 5-year disease free survival and overall survival after both treatment strategies.To determine stoma-free survival at one, three and five years for both groups of patients.To investigate the impact of organ preserving therapy on HRQol and functional outcomes compared to radical surgery.Determining cost-effectiveness of rectal preserving therapy with intensified follow-up using MRI and endoscopy.

### Study procedures

Since the control arm consists of completion TME which will remove the mesorectum, the investigational arm consists of chemoradiotherapy which is primarily targeted at the mesorectum without expansion to pelvic sidewall and lymph nodes along the iliac vessels. This is based on the hypothesis that potential lymph node metastases are located close to the primary tumour site in these early stage cancers. Adapting radiation fields that are normally used in more advanced rectal cancer limits toxicity based on a patient tailored approach according to estimated recurrence risks. Patients will receive 25×1.8 Gray, 5 days a week, combined with Capecitabine 825 mg/m2 twice a day, which will not be continued during the weekends. The treatment in both study arms should start between 4-8 weeks after local excision. Patients treated with adjuvant chemoradiotherapy in the experimental arm will receive an intensified follow-up schedule with four extra pelvic MRI’s and three extra sigmoidoscopies in addition to routine follow-up according to the Dutch colorectal cancer guideline, while control patients undergo routine follow-up with one additional pelvic MRI at 24 months (see Fig. 1).

**Fig. 1 Fig1:**
[figure not shown]
Study flowchart

### Patient population

Patients who are diagnosed with early rectal cancer that was locally excised with tumour free margins (≥1 mm) and a carcinoma within 10 cm from the anal verge are informed about the TESAR trial if histopathology reveals the following characteristics: pT1 with a diameter of 3–5 cm, or pT1 with a maximum diameter of 3 cm and at least poor differentiation and/or lymphatic and/or venous invasion and/or SM3 invasion depth, or a pT2, maximum size 3 cm, well/moderately differentiated and without lymphatic or venous invasion (Fig. 2). Any endoluminal technique for local excision may be included (TEM, TAMIS, TSPM, EMR, ESD or polypectomy). A central review of the pathology will be performed in order to verify the histological inclusion criteria. Furthermore, clinical nodal status should be N0 by pelvic MRI. In order to prevent overstaging by post-excision MRI in these early rectal cancers, mesorectal and extra-mesorectal lymph nodes with a size smaller than 10 mm will be interpreted as benign independent of their morphologic features. Other inclusion criteria are absence of distant metastasis by CT thorax/abdomen, age > 18 years, life expectancy of at least 12 months, WHO performance status 0–2, and written informed consent.

**Fig. 2 Fig2:**

Inclusion characteristics

Patients are excluded from the study or registry in case of a proximal rectal cancer (>10 cm from the anal verge or requiring partial mesorectal excision), not fulfilling pathology or imaging inclusion criteria, previous pelvic irradiation, concomitant malignancies within past 5 years, or if patients are unfit for subsequent chemoradiotherapy or surgery.

Early rectal carcinoma’s with pathological features showing low risk T1 (<5 cm, well differentiated, no lymphatic or vascular invasion) or high risk T2 (>3 cm and/or poorly differentiated and/or lymphatic or vascular invasion) will be asked for registration only and will be asked to sign informed consent to collect to use the paraffin specimen for translational studies.

### Outcome parameters

Loco-regional recurrence, morbidity, disease free survival, stoma free survival and overall survival will be assessed by regular follow-up at 3, 6, 9, 12, 18, 24, 36, 48 and 60 months post-operatively. Morbidity will be assessed using the Comprehensive Complication Index (CCI) for the patients that undergo TME surgery and the NCI CTCAE Toxicity Criteria (v4) for patients in the adjuvant chemoradiotherapy arm [22]. Health related quality of life and functional outcomes will be measured using the EQ-5D, EORTC QLQ C29 & C30 and the LARS score. Possible advantage of the new rectal preserving treatment in cost per quality of life adjusted life years using the EQ5D score will be analysed. The total costs will be assessed by summing the procedure related costs, in hospital stay costs, re-intervention and morbidity related costs and time to return to work will be calculated in loss of work days, which can be converted to costs.

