### Data analysis

All analyses will be on an intention-to-treat basis [23]. Patients will be analysed as they are randomized irrespective of the treatment actually received. The intention-to-treat population will include all patients who have given their informed consent and for whom there is confirmation of successful allocation of a randomisation number. To substantiate the interpretation of the intention-to-treat analysis a per protocol analysis will also be performed.

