Statistical analyses will be performed using SPSS software for Windows version 23 or higher. The one-sided 95 % confidence interval for the between-group difference in locoregional recurrence corresponds to the lower limit of the two-sided 90 % confidence interval for this difference (experimental minus standard). The organ preserving treatment group (intervention) is considered to be non-inferior to the standard treatment group if the one-sided 95 % confidence for the difference in loco-regional recurrence excludes a difference of minus 7 percentage points or farther away from zero in the same direction. For the secondary outcomes as disease free survival and overall survival two-sided 95 % confidence intervals will be calculated. Appropriate summary descriptive statistics will be determined for all secondary endpoints at each visit using raw scores. To assess morbidity the continuous scale of the Comprehensive Complication Index [22] and the categorical Clavien-Dindo classification will be used, for which appropriate statistical tests will be undertaken (the Mann Whitney *U* test, in case of non-normal distribution, and the Chi squared test respectively). For continuous secondary endpoints, either analysis of variance or analysis of covariance models will be used and where necessary, the repeated measures procedure will be implemented. Quality of life data (e.g. EORTC-C30, EORTC-CR29, LARS and EQ-5D) will be graphically represented across all time points and analysed using a repeated measures analysis of variance. All tests based on proportions will be analysed using a logistic regression model with treatment as a factor and, where appropriate, other specified covariates. Time-to-event will be analysed with use of Kaplan-Meier Survival analysis and compared using the log-rank test. The secondary efficacy analysis will be based on the Full Analysis Set (FAS) and the per protocol populations. Significance level is set at an alpha of 0.05 and no adjustment will be made for testing multiple secondary outcomes. Some significant findings are expected to occur by chance so undue consideration will not be given to any particular significant difference. Moreover, interpretation of the results will be based on patterns of differences and in conjunction with the results of the primary analyses.

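### Outcome parameters and Data analysis conflict on morbidity: a different instrument is assigned to each treatment, but the planned tests need the same instrument in both arms

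*Protocol article*

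**What the plan says.** Methods/Design hypothesises that local excision plus chemoradiotherapy with close surveillance is non-inferior on local recurrence and "superior in terms of treatment related morbidity, functional outcome, and HRQoL". The first secondary aim is "To compare treatment related morbidity between the study arms, both short and long-term".

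Outcome parameters assigns the instruments: "Morbidity will be assessed using the Comprehensive Complication Index (CCI) for the patients that undergo TME surgery and the NCI CTCAE Toxicity Criteria (v4"). The second of these, CTCAE, applies to the chemoradiotherapy arm. The first group is defined by the operation a patient undergoes, the second by arm. The section names no morbidity measure that applies to everyone.

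Data analysis states: "To assess morbidity the continuous scale of the Comprehensive Complication Index [22] and the categorical Clavien-Dindo classification will be used". The tests are the Mann-Whitney U test for the CCI, "in case of non-normal distribution, and the Chi squared test respectively", the latter for Clavien-Dindo. CTCAE does not appear in that section, and Clavien-Dindo does not appear in Outcome parameters. The analysis principle is intention-to-treat: "Patients will be analysed as they are randomized irrespective of the treatment actually received".

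**The concern.** A two-sample test needs the same variable measured in both samples. The outcome section gives the chemoradiotherapy arm a toxicity scale that the analysis section does not name. The analysis section tests two surgical-complication scales that the outcome section does not assign to that arm as randomised. No mapping between the scales is given.

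At stake is the morbidity part of the superiority hypothesis. The Background calls for a balance between treatment-related morbidity and oncological control, and the Discussion presents less morbidity as an expected benefit. If events in the two arms are graded on different scales, that side of the balance has no randomised estimate. A later analysis plan cannot recover grades that the case-report form did not collect.

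**Working it through.** **1. The plan's own design figure (context only).** No figure is stated for morbidity; the group size of 151 is used below, so it is checked first. Inputs from Sample size: 98% and 96% free of local recurrence, margin 7 points, power 80%, drop-out 5%. The one-sided 5% level comes from Data analysis.

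- n per arm = (1.645 + 0.842)² × (0.98 × 0.02 + 0.96 × 0.04) / (0.07 − 0.02)² = 6.183 × 0.058 / 0.0025 ≈ 143.4, rounded up to 144.
- With drop-out: 144 / 0.95 = 151.6, so 152 per arm and 304 in total. The plan states 302 (151 per arm). Rounding only at the end gives 143.4 / 0.95 ≈ 151.

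The figure reproduces and does not depend on how morbidity is measured.

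**2. The sections side by side.**

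| Instrument | Assigned in Outcome parameters to | Named test in Data analysis |
|---|---|---|
| CCI | patients who undergo TME | Mann-Whitney U |
| Clavien-Dindo | not listed | chi-squared |
| CTCAE v4 | chemoradiotherapy arm | none |

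No row has both an assignment to all randomised patients and a named test.

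**3. Who would have a CCI value if the outcome section is followed literally.**

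- Control arm: those who undergo TME, at most 151. A control patient who does not undergo TME has neither instrument.
- Experimental arm: only those who later undergo TME. Assume that every local recurrence leads to TME and that nobody else in the arm has it; the document gives no figure for either.
  - At the expected 96% free of recurrence at three years: 151 × 0.04 = 6.04, about 6 patients.
  - At the non-inferiority limit of 91% free of recurrence: 151 × 0.09 = 13.59, about 14 patients.

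**4. What the comparison would then be.** Up to 151 control patients would be set against about 6 to 14 experimental patients who enter because their disease recurred. That subset is selected by an outcome after randomisation, so the contrast is not a randomised one. It also leaves out the chemoradiotherapy toxicity of the remaining patients (about 137 to 145 of 151), which sits on the other scale.

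**The case against.** The strongest reply is that Data analysis does not limit the CCI or Clavien-Dindo to one arm. Since it plans two-group tests on them, it can be read as grading both arms, with CTCAE as extra toxicity detail; Outcome parameters does not say that each instrument is used exclusively. The article condenses a fuller protocol that is not shown. This stands to the extent that the point is a contradiction between two sections, not proof that the data will be absent. It does not remove the point: on that reading the outcome section is wrong as written, and the two must still be reconciled.

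The general provisions in Data analysis could also cover CTCAE: descriptive statistics for all secondary endpoints, and logistic regression for proportions. That would allow a proportion above some toxicity grade to be analysed, but the outcome section gives the control arm no CTCAE grades to compare it with.

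On intention-to-treat, the rule governs how patients are analysed, not which form records an event. Complications of salvage TME can be counted in the arm of randomisation. So the instrument split does not by itself breach the rule. What remains is that control patients without TME have no named instrument.

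Three stronger readings are tempting and are not supported:

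- **That the experimental arm has no CCI data at all.** Salvage TME would supply a few values.
- **That the missing values would be entered as zero, guaranteeing a significant result.** The document plans no such rule. The 36% operative morbidity in the Background describes radical rectal surgery in the literature; it is not a projected control-arm rate for this trial.
- **That lower morbidity is the stated reason for accepting more recurrences.** The Discussion attributes that acceptance to close follow-up with early salvage.

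**Conclusion.** The point holds as a conflict between Outcome parameters and Data analysis on a secondary outcome. Followed as written, the outcome section cannot supply a valid randomised comparison for the morbidity aim and hypothesis in Methods/Design, because no common scale is collected. The CCI data in the experimental arm would come from about 6 of 151 patients at the expected recurrence rate, or about 14 at the limit. These counts rest on the assumption that every recurrence, and nothing else, leads to TME, and on the three-year recurrence figures; they illustrate the scale and are not predictions.

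A reader might infer that the trial's case as a whole is undermined. It is not. The primary endpoint, margin and sample size are untouched. The functional and quality-of-life parts of the superiority hypothesis use instruments that are not split by arm. The correction is worth making early, because ungraded events are hard to reconstruct later, but it does not bear on the primary conclusion.

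**What to change.** Reconcile the two sections as follows:

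- In Outcome parameters, name at least one morbidity scale graded in all patients of both arms, including control patients who do not undergo TME. Either CCI/Clavien-Dindo or CTCAE would serve, provided it is applied to treatment toxicity and surgical complications alike.
- Use the same observation window from randomisation in both arms, with separate short-term and long-term windows if both are to be compared.
- In Data analysis, base the between-arm test on that common scale, by randomised arm, with salvage-surgery complications counted in the arm of randomisation.
- Keep the other instrument as treatment-specific description, and say so.

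Which scale is made common, and whether the test uses a continuous score or a grade threshold, is a choice for the trial team. The cost is one additional grading of events on the case-report form. No new procedure or visit and no change in sample size is needed.

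### LARS is to be compared by intention to treat, but a patient with a stoma has no LARS score, so that one comparison would rest on controls selected after randomisation

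*Protocol article*

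**What the plan says.** In Methods/Design, the trial's hypothesis is that rectal preservation is non-inferior for local recurrence and "superior in terms of treatment related morbidity, functional outcome, and HRQoL".

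Outcome parameters names four instruments for quality of life and function: "Health related quality of life and functional outcomes will be measured using the EQ-5D, EORTC QLQ C29 & C30 and the LARS score".

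Data analysis fixes the population, "All analyses will be on an intention-to-treat basis", with a supporting per-protocol analysis. It also fixes the method, which is an ANOVA: "Quality of life data (e.g. EORTC-C30, EORTC-CR29, LARS and EQ-5D) will be graphically represented across all time points and analysed using a repeated measures analysis". It does not say how a patient with a stoma enters the LARS analysis.

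On how often that will happen, the Background describes radical rectal surgery as low anterior resection (LAR) or abdominoperineal resection (APR). It reports from an earlier TME trial that "19 % of patients did not have a reversal of a temporary stoma after LAR and the overall long term or permanent stoma rate was 40" per cent. Patient population admits tumours up to 10 cm from the anal verge and excludes those needing only a partial mesorectal excision, so controls are planned for full TME. Stoma-free survival at one, three and five years is a separate secondary aim for both arms.

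**The concern.** The article does not define the LARS score. I take it to rate bowel function in patients who pass stool through the anus, and the point rests on that reading. A patient with an end stoma, an unreversed stoma or a protective stoma still in place then has no score. The value does not exist because of the treatment given, which is different from a questionnaire that was not returned.

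The two arms differ sharply in this. Experimental patients keep the rectum unless they need salvage surgery or cross over. Controls have a TME, and some of them will have a stoma for a time or for life. A LARS analysis that uses the available scores therefore compares nearly all of one randomised group with the part of the other that kept or regained continuity. That is not an intention-to-treat comparison, although the article says every analysis is one.

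The Discussion accepts a slightly higher recurrence risk in the experimental arm, and the expected return is better morbidity, function and quality of life. A bowel-function result that is hard to interpret weakens that part of the argument.

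**Working it through.** **The plan's own sample size.** Inputs from Sample size and Data analysis: 98% and 96% free of local recurrence, margin 7 points, one-sided 5% (from the one-sided 95% interval), 80% power, 5% drop-out.

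- Variance: 0.98 × 0.02 + 0.96 × 0.04 = 0.058.
- Distance to the margin: 0.07 − 0.02 = 0.05.
- n per arm = 0.058 × (1.645 + 0.842)² / 0.05² ≈ 143.4.
- With drop-out: 143.4 / 0.95 ≈ 151.0 per arm, 302 in total.

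The stated 302 is reproduced, and nothing below changes it. The article states no effect size or power for LARS.

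**Controls with a LARS score.** Evaluable per arm: 151 × 0.95 = 143.45, taken as 143. Scorable controls = 143 × (1 − s), where s is the share with a stoma at the visit. The 40% is the Background figure from the earlier trial; 20% is an assumed lower value.

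| s | scorable | without a score |
|---|---|---|
| 20% | 143 × 0.80 = 114.4 | 28.6 |
| 40% | 143 × 0.60 = 85.8 | 57.2 |

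**Experimental patients without a score.** The plan expects 100 − 96 = 4% local recurrence at three years. If every one of these had salvage surgery that left a stoma, 143 × 0.04 = 5.7, about 6 patients, would have no score. Crossover to TME would add some. The loss is clearly unequal between arms.

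**How far the control mean could move.** This is an illustration, not an estimate. Suppose bowel function is a standard normal latent score and the fraction s with a stoma is missing. If these are exactly the worst patients, the observed control mean improves by φ(Φ⁻¹(s)) / (1 − s). With correlation ρ between latent function and having a stoma, multiply by ρ.

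| s | ρ = 1 | ρ = 0.5 | ρ = 0 |
|---|---|---|---|
| 20% | 0.35 SD | 0.17 SD | 0 |
| 40% | 0.64 SD | 0.32 SD | 0 |

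The document gives no value for ρ. The result runs from no bias to a large one.

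**Precision.** Detectable difference at 80% power, two-sided 5% = (1.960 + 0.842) × √(1/143 + 1/n₂).

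- No loss, n₂ = 143: 0.33 SD.
- 20% loss, n₂ = 114.4: 0.35 SD.
- 40% loss, n₂ = 85.8: 0.38 SD.

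The loss of precision is modest. The larger problem is which patients are compared.

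**The named model.** Classical repeated measures analysis of variance uses patients with a value at every visit. If LARS is measured while protective stomas are in place, a control with a temporary stoma at one visit is lost from all visits. In the plotted means, controls would instead enter as stomas close, so the curve would move partly because the sample changes. The article's text gives no LARS schedule, so both consequences are conditional on early measurement.

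**The case against.** The strongest objection is that the article is merely silent. Nowhere does it say that patients with a stoma are dropped, and the handling of one secondary questionnaire is commonly left to a full protocol or analysis plan that is not shown. That stands as far as detail goes. But the article does fix the instrument, the population and the model, and these do not fit together for a score that does not exist in part of one arm. An ordinary missing-data rule does not settle this; someone has to choose what is being estimated.

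Other objections stand and set the limits of the point:

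- A reader might infer that the whole functional superiority hypothesis is tested on selected controls. The document does not support this. EQ-5D and the EORTC questionnaires can still be collected from patients with a stoma, and stoma-free survival counts the stoma in every randomised patient.
- A reader might take 40% as the rate expected in this trial. It is a background figure from an earlier one.
- A reader might assume that patients with a stoma have the worst function. An APR may simply follow from a low tumour, and the document gives no function data by stoma status.
- A reader might put a number on the bias by counting every stoma as poor bowel function. With assumed poor-function rates of 50% in controls without a stoma and 30% in the experimental arm, a 20-point difference becomes 0.40 + 0.60 × 0.50 − 0.30 = 40 points. That jump comes from changing the endpoint. It does not measure a bias.
- The use of raw scores is stated for the descriptive summaries, not for the comparative model, and should not be held against the latter.
- Data analysis says secondary results will be read as patterns and that no single significant difference will be given undue weight. This lowers the stakes, but it does not make the LARS contrast a randomised one.
- Ranking a stoma as the worst state builds into the functional score an outcome already reported separately, and it favours the experimental arm. This is a fair criticism of using that ranking as the only analysis.

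**Conclusion.** The concern holds for the LARS component alone. As planned, the LARS contrast is conditional on bowel continuity, a post-randomisation state that treatment affects and that differs between arms. At an assumed stoma share of 20 to 40%, about 114 to 86 of 143 evaluable controls could be scored, while few experimental patients would be lost.

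If patients with a stoma have poorer bowel function, the contrast understates the experimental benefit. The document does not allow the size to be estimated, and it could be nil. Because this bias would work against the experimental arm, the main risk is a missed or uninterpretable benefit rather than a false claim of superiority.

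The conclusion rests on two assumptions: that LARS applies only to patients with continuity, and that a stoma share somewhere in the range suggested by the Background carries over to this trial. The amendment is worth making because the LARS result as planned should not carry the bowel-function claim.

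**What to change.** Do not base the superiority claim on bowel function on an analysis of variance of LARS alone. Instead:

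1. At fixed time points, add an ordered outcome covering all randomised patients: no LARS, minor LARS, major LARS, stoma in place. Compare arms by proportional odds or a rank method. Questionnaires that are simply not returned still need an ordinary missing-data rule.
2. Add one sensitivity analysis that ranks a stoma level with major LARS.
3. Keep LARS among patients with bowel continuity, but label it conditional and descriptive. Report it beside stoma-free survival, with the number of patients with a stoma per arm at each visit.
4. Base the superiority claim on quality of life on scales defined with and without a stoma (C30, EQ-5D).

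Stoma status and LARS are already to be collected, so the cost is analysis wording and a little more analysis work. The sample size does not change. The downside is that the rank given to a stoma is a value judgement, which is why the second ranking is needed and why the conditional result should stay visible.
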